### Recruitment {15}

The recruitment will follow a convenience sampling strategy. To aim for a student population with diverse academic backgrounds, participants will be recruited broadly through social media platforms, email lists, and flyers at the research university where the experiment will be conducted. Given that the experiment will start during the summer, the research team can recruit summer school students as participants. Thus, the study sample will not be limited to the students presently at the university. The recruitment materials include a brief description of the study, the eligibility criteria for participation, and the compensation for participation. Individuals who are interested in participation can sign up on a calendar by selecting available time slots provided by the experimenters. Participants will receive 30 euros in compensation upon completion of the experiment. Participants who withdraw in the middle of the experiment will receive partial compensation, prorated based on the amount of time they spend in the experiment.

## Assignment of interventions: allocation

### Sequence generation {16a}

The sequence will be generated using computer-generated random numbers to assign participants in a 1:1 ratio to the intervention group or the control group. The randomization process will be independent of the recruitment and implementation process. Only participants who fulfill the eligibility criteria and give consent to participate in the study will be allocated to the randomized sequence.

### Concealment mechanism {16b}

Not applicable. The randomization procedures are covered in Sects. 16a, 16c, and 17a.

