### Who will take informed consent? {26a}

Before the experiment starts, the participant will be given an information sheet and a consent form by the experimenter. The information sheet will explain the study’s aim, procedures, potential risks and benefits, compensation, and contact information of the study investigators. The experimenter will answer any questions that the participant may have before asking for consent. If the participant meets the inclusion criteria and agrees to participate, they will be asked to sign the consent form, which the experimenter will countersign. The participant will receive the information sheet and a copy of the consent form. The other copy of the consent form will be retained by the research team. All participants will be verbally informed that they can withdraw from the study at any time without giving any reason and without having any negative consequences to their academic studies.

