### Implementation {16c}

Randomization was generated in advance of the entire experiment using an R script that allocated participant IDs into either the intervention group or the control group. The randomization algorithm is independent of the researchers who will recruit participants and implement the protocol.

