## Assignment of interventions: blinding

### Who will be blinded {17a}

Participants will be blinded to the randomization process but not to the intervention itself. Specifically, participants are not informed that the study involves a randomized controlled trial or that there are different experimental conditions. As such, they are unaware of whether they have been assigned to a control or intervention group. However, blinding to the intervention is not feasible in this context: participants in the intervention group are explicitly instructed to use ChatGPT during the writing task. Experimenters will not be blinded because they need to set the computer screen to the appropriate format depending on whether the participant is assigned to the intervention group or the control group. The analyst will be blinded, and the assignment condition will be masked from the analyst to minimize potential biases from statistical analysis.

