### Procedure for unblinding if needed {17b}

Unblinding participants to the randomization process is not permissible because it may introduce social desirability bias. That is, if participants are aware that they are assigned to the intervention group, they may act differently to align with expectations of the experimenter. The participant’s data will be excluded if the assigned condition is accidentally revealed and will not be counted in the randomized sequence.

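### Allocation concealment is declared not applicable and no listed section hides the next arm; separately, allocated participants can be dropped from the sequence, against the intent-to-treat analysis

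*Protocol article*

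**What the plan says.** All references are to the protocol article.

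- Concealment mechanism {16b}: "Not applicable. The randomization procedures are covered in Sects. 16a, 16c, and 17a".
- Sequence generation {16a}: "The randomization process will be independent of the recruitment and implementation process". It adds that people enter the sequence only once they are eligible and have consented.
- Implementation {16c}: the list was made before the experiment by a script that "allocated participant IDs into either the intervention group or the control group", and "The randomization algorithm is independent of the researchers who will recruit participants and implement the protocol".
- Who will be blinded {17a}: "Experimenters will not be blinded because they need to set the computer screen to the appropriate format". The analyst is to be masked.
- Who will take informed consent? {26a}: the experimenter hands over the information and the form. If eligible and willing, participants sign: "they will be asked to sign the consent form, which the experimenter will countersign".
- Recruitment {15}: participants choose among time slots that the experimenters offer.
- Procedure for unblinding if needed {17b}: a participant's data are excluded "if the assigned condition is accidentally revealed and will not be counted in the randomized sequence".
- Statistical methods for primary and secondary outcomes {20a}: both primary outcomes are analysed by intent to treat.

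**The concern.** Concealment and blinding do different jobs. Concealment protects the assignment up to the moment a person is enrolled; blinding protects what follows. Lack of blinding is no reason to do without concealment, and makes it more useful.

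Here a complete ID-to-arm list exists before the first session, and the staff who take consent must learn the arm at some point in order to set the screen. If they can learn it before enrolment is settled, a decision to enrol, defer or turn someone away could depend on the arm. The trial's causal claim rests on randomisation, so this should be closed off by a stated procedure.

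The rule in {17b} raises a second, distinct issue. It acts after allocation, so concealment would not cure it. It takes people out of the randomised set that the intent-to-treat analysis is meant to keep whole.

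**Working it through.** The point is settled by reading the sections together; it depends on no figure in the document.

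**Step 1. Do the cross-referenced sections supply concealment?** A mechanism has to say who holds the list, when an arm is released, and what stops the enrolling person from seeing it earlier.

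| Section | Who holds the list? | When is the arm released? | What hides the next arm? |
|---|---|---|---|
| {16a} | Not stated | Entry to the sequence follows eligibility and consent; disclosure to staff is not addressed | Independence asserted, no means given |
| {16c} | Not stated | Not stated; the list predates the experiment | Independence of the algorithm only |
| {17a} | Not stated | Not stated; experimenters need the arm to set the screen | Nothing |

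Independence of the algorithm describes how the list was made, not who can read it. The order in {16a} says when a person joins the sequence. It does not say that the arm waiting for the next ID is unknown until then.

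**Step 2. Does the gap touch people who can influence enrolment?** Three tasks are expressly given to experimenters: offering slots {15}, giving and countersigning consent {26a}, and setting the screen by arm {17a}. Trial design {8} has one participant at a time. If IDs are issued in list order (an assumption; the protocol does not say), anyone with the list knows the next arm.

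**Step 3. Is {17b} compatible with {20a}?** An intent-to-treat analysis keeps participants in the arm to which they were allocated. Under {17b}, someone already allocated loses both their data and their place in the sequence because of an event after allocation. Both rules cannot apply to the same participant.

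**Step 4. Can the size be worked out?** No. The document gives no rate of deferral or exclusion and no link between such decisions and outcome. The following shows only how the planned test would respond to an assumed imbalance. Inputs are 160 participants at 1:1, so 80 per arm; SD 1 as in Sample size {14}; two-sided alpha 0.025 from {20a}; and a true effect of zero.

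- Standard error = √(2/80) = 0.158; critical value z = 2.241.
- With an imbalance of b SD, the rejection rate is 1 − Φ(2.241 − b/0.158) + Φ(−2.241 − b/0.158).
- b = 0.05 gives 3.2%; 0.10 gives 5.6%; 0.20 gives 16.5%; 0.30 gives 36.5%.

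None of these values of b has support in the protocol, so they do not measure this trial's bias.

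**The case against.** The best reply is {16a}. It says the process is independent of recruitment and implementation, and it places eligibility and consent before entry to the sequence. Trial design {8} agrees: consent comes in the first stage and the computer in the second. This lowers the risk and leaves only the enforcing mechanism missing. That much stands, but an order of events is not concealment if the next arm can already be seen. Nor can the mechanism be presumed to sit elsewhere: section {31c} calls this document the full protocol, and {16b} makes a positive statement that concealment does not apply.

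A reader might infer several stronger things that the document does not support:

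- That experimenters know the arm before consent. No section says so; the point is that none prevents it.
- That experimenters screen participants and decide same-day exclusions, for example under the alcohol rule. Eligibility criteria {10} and section {17b} name no decision-maker.
- That a particular share of the planned effect is at risk. Any such figure needs invented exclusion rates. Writing, English and critical-thinking ability are recorded only in the post-survey {18a}, so the experimenter has no recorded ability data at consent.
- That no analysis could detect or correct the bias. The adjustment in {20a} for three skill measures and motivation could reveal or partly correct an imbalance. It is a limited safeguard: the skill items are self-reported after the task, and people turned away contribute no data.

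It is also fair to say that influence after allocation is restrained by design: participants work alone {11c} and essays are scored automatically {12}.

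**Conclusion.** The point holds in this form. Declaring concealment not applicable is wrong, and the sections cited in its place contain no means of hiding the next assignment from staff who take consent and must learn the arm. Followed as written, the trial has no stated protection against foreknowledge. This is an open risk, moderated by the order in {16a}. It is not evidence that selection took place, and no magnitude can be attached to it from the document. The conclusion rests on the roles expressly given to experimenters and on the absence of any statement about custody or release of the list.

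The conflict between {17b} and {20a} needs no assumption: one section excludes allocated participants and the other promises to analyse by intent to treat. How many participants it would affect cannot be told from the document. Both matters should be corrected.

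**What to change.** 1. In {16b}, replace the present answer with a rule. The list is held by someone who neither recruits nor runs sessions; the data manager named in {5d} is one candidate. The arm for each ID is released, for example through the survey platform already in use, only after eligibility is confirmed and consent signed. The screen is set after release.
2. Amend {17b} so that every released ID counts as randomised and stays in the intent-to-treat set. Exclusion of participants whose condition was revealed becomes a sensitivity analysis only.

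The cost is a small set-up task with existing staff and software, and an estimated minute per session. If a safeguard of this kind already operates, describing it in {16b} takes a sentence, and only {17b} needs a change of rule.

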### Implementation {16c}

Randomization was generated in advance of the entire experiment using an R script that allocated participant IDs into either the intervention group or the control group. The randomization algorithm is independent of the researchers who will recruit participants and implement the protocol.

## Assignment of interventions: blinding

### Who will be blinded {17a}

Participants will be blinded to the randomization process but not to the intervention itself. Specifically, participants are not informed that the study involves a randomized controlled trial or that there are different experimental conditions. As such, they are unaware of whether they have been assigned to a control or intervention group. However, blinding to the intervention is not feasible in this context: participants in the intervention group are explicitly instructed to use ChatGPT during the writing task. Experimenters will not be blinded because they need to set the computer screen to the appropriate format depending on whether the participant is assigned to the intervention group or the control group. The analyst will be blinded, and the assignment condition will be masked from the analyst to minimize potential biases from statistical analysis.

### Procedure for unblinding if needed {17b}

Unblinding participants to the randomization process is not permissible because it may introduce social desirability bias. That is, if participants are aware that they are assigned to the intervention group, they may act differently to align with expectations of the experimenter. The participant’s data will be excluded if the assigned condition is accidentally revealed and will not be counted in the randomized sequence.

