### Explanation for the choice of comparators {6b}

In the control group, as in the intervention group, the computer screen will be set up in a split-screen format. On the left side of the screen, the participant will receive the same instructions on the writing prompt, writing requirements, time requirements, grading feedback, and the grading rubric. Additionally, the instructions will highlight to the participant that they can use a text editor in any way they like to assist their writing. On the right side, instead of ChatGPT, a basic text editor interface will be displayed. In summary, this comparator will keep the split-screen format consistent between the two groups and ensure that participants in the control group will complete the writing task with minimal support.

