## Statistical methods

### Statistical methods for primary and secondary outcomes {20a}

Here, the intervention effect on the two primary outcomes will be estimated by an intent-to-treat analysis. Our first primary outcome, writing performance, will be treated as a continuous variable. Our second primary outcome, cognitive effort as measured by mean changes in pupil size, will also be treated as a continuous variable. We will estimate the intervention effect on each outcome separately using ordinary least squares (OLS) regression with heteroskedasticity-robust standard errors. To control for type I error inflation due to multiple testing, we will apply a Bonferroni correction. Accordingly, the adjusted significance threshold is set at *α* = 0.05/2 = 0.025. The outcome of cognitive effort is a psychophysiological measure recorded throughout the entire writing process. Standard pre-processing steps will be taken before the statistical analysis [51, 52], such as correcting for screen angle distortion, removing invalid data that do not reflect the actual pupil size (pupil size below 1.5 mm or over 9 mm [53], often due to blinking), smoothing to remove small oscillatory and noise activity, interpolating blink related invalid data, downsampling, and correcting pupil size changes based on the baseline pupil size that will be collected during a 30-s relaxation task at the beginning of the experiment. Participant-level data will be excluded if the data do not meet basic quality standards, such as having a high proportion of invalid data.

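### Excluding randomised participants whose condition is revealed contradicts the intent-to-treat analysis promised for both primary outcomes

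*Protocol article*

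**What the plan says.** All references are to the protocol article.

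- **Analysis principle (20a).** The plan states that "the intervention effect on the two primary outcomes will be estimated by an intent-to-treat analysis". The two outcomes are the writing score and the mean change in pupil size.
- **Who is randomised (16a, 16c).** "Only participants who fulfill the eligibility criteria and give consent to participate in the study will be allocated to the randomized sequence". The list was fixed beforehand: "Randomization was generated in advance of the entire experiment using an R script that allocated participant IDs".
- **Reveal rule (17b).** A participant's "data will be excluded if the assigned condition is accidentally revealed and will not be counted in the randomized sequence". The reason given is social desirability: "if participants are aware that they are assigned to the intervention group, they may act differently to align with expectations of the experimenter".
- **Blinding (17a).** "Experimenters will not be blinded because they need to set the computer screen to the appropriate format". Participants are not told that there are different conditions. The analyst is masked to assignment.
- **Pupil quality (20a).** After the list of pupil pre-processing steps: "Participant-level data will be excluded if the data do not meet basic quality standards, such as having a high proportion of invalid data".

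**The concern.** Intent-to-treat means that everyone randomised is analysed in the assigned arm. The reveal rule takes some of them out afterwards, for both primary outcomes, and also takes them out of the count of the sequence. Nothing in the article reconciles the two statements. A later analysis plan could not obey both; it would have to override one.

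The rule is also open-ended. It does not say what counts as a reveal, who decides, or up to what point in the session it applies, so it could be invoked after the essay is written. Because its rationale is stated only for the intervention group, uneven use across arms is foreseeable. If those removed differ in writing or in effort from those kept, the comparison loses the protection of randomisation.

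A lesser ambiguity lies beside it. The pupil-quality sentence speaks of participant-level data without saying for which outcome, so a reader cannot be certain that a valid essay score is kept when the pupil recording fails.

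**Working it through.** **1. Order of events.** Only eligible, consenting people enter the sequence (16a), and the sequence assigns participant IDs in advance (16c). A condition can be revealed only once it has been assigned. The exclusion in 17b therefore always falls on someone already randomised, and applying it gives a set that is not the intent-to-treat set of 20a.

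**2. Can the exclusion be related to arm?**
- Experimenters know the arm (17a) and are the participant's contact by intercom (11c). That a reveal would usually come to light through them is an inference; no assessor is named.
- The rationale in 17b mentions only awareness of being in the intervention group.
- Masking the analyst (17a) does not protect against this, because the exclusion can be made before the analyst receives the data.

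These points make a difference between arms possible. They do not show that one would occur.

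**3. The plan's own figure.** The sample size section gives 160 participants for d = 0.45, alpha 0.05 and power above 0.8. Taking the test as two-sided (not stated), the normal approximation gives 78 per arm, or 156 in total, and power at 80 per arm is 0.81. The stated figure reproduces. It is used here only for the scale of the effect and for 80 per arm.

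**4. Size of a possible shift.** Let *e* be the share removed from one arm and *g* the difference, in SD, between the mean of those removed and the mean *m* of those kept.

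Full-arm mean = (1 − *e*)·*m* + *e*·(*m* + *g*) = *m* + *e*·*g*

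Analysing only those kept moves that arm's mean by *e*·*g* in absolute value. With removals in both arms, the net shift is the difference of the two products, and it is zero if they are equal.

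The documents give neither *e* nor *g*, so the values below are assumptions, with removal from one arm only. Type I error at the plan's threshold of 0.025 uses the normal approximation with SD 1, SE = √(1/[80(1 − *e*)] + 1/80), and 1 − Φ(2.241 − *eg*/SE) + Φ(−2.241 − *eg*/SE).

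| *e* (of 80) | *g* | shift *e*·*g* | share of 0.45 | type I error at 0.025 |
|---|---|---|---|---|
| 5% (4) | 0.5 | 0.025 | 6% | 0.027 |
| 10% (8) | 0.5 | 0.05 | 11% | 0.032 |
| 10% (8) | 1.0 | 0.10 | 22% | 0.054 |
| 15% (12) | 1.0 | 0.15 | 33% | 0.092 |

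The comparison with 0.45 applies to the writing score only; the sample size section reports no prior effect size for the pupil outcome.

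**5. Pupil-quality sentence.** It closes the paragraph on pupil pre-processing, after blink removal, interpolation and baseline correction. Its natural scope is the pupil analysis. An unusable recording is then a missing outcome and not a breach of analysis by assigned arm. Only the stated scope needs to be made explicit.

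**The case against.** The best defence is that the event should be rare. Sessions are run one participant at a time, instructions are on screen, and the participant is alone in the room. The plan gives a reason for the exclusion, declares an exploratory framework and masks the analyst. The bias range rests wholly on assumed values, takes removals from one arm only and has no argued direction. All of that is fair. It limits the likely size but does not remove the contradiction over who is analysed.

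Some stronger readings are tempting and are not supported:

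- **Replacement.** A reader might infer that not being counted in the sequence means the slot is refilled. No section describes such a step.
- **Hidden exclusions.** A reader might infer that removed participants would vanish from the participant flow diagram. The article does not address flow reporting.
- **Arm-related pupil loss.** The screens differ by arm ("On the right side, instead of ChatGPT, a basic text editor interface will be displayed"), and a reader might suppose that controls look at the keyboard more and lose more pupil data. Nothing in the documents says so; the intervention arm may use ChatGPT as it likes and types too.
- **Missing pupil cut-off.** A numerical threshold is detail that a condensed article may leave to the fuller documents.
- **Lost power.** No exclusion rate is given from which to compute a loss, and power at the 0.025 threshold is a separate question.

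**Conclusion.** The point holds in a limited form. Sections 17b and 20a contradict each other as written: following the reveal rule means the primary analysis is not intent-to-treat for either primary outcome. The exclusion has no criterion or time limit, staff who know the arm could influence it, and its rationale is one-sided, so selection related to arm is possible.

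Its size cannot be derived from the documents and may be close to nothing if reveals are rare or fall equally on both arms. The range of 0.025 to 0.15 SD depends on two assumptions: 5% to 15% removed from one arm only, and a difference of 0.5 to 1.0 SD between those removed and those kept. It shows what the rule could do and does not predict what it will do. The pupil-quality sentence needs only a clarification of scope.

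**What to change.** Replace the exclusion rule in 17b. Every randomised participant stays in the sequence and in the primary intent-to-treat analysis in the assigned arm. Cases in which the condition was revealed are flagged, excluded only in a sensitivity analysis, and reported by number in each arm. In 20a, state that the pupil-quality exclusion applies to the pupil outcome only and that the essay score is kept.

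The cost is a change of wording and one sensitivity analysis; the planned 160 participants are unaffected. The downside is that a few participants with possible demand effects remain in the primary set. The sensitivity analysis addresses the social desirability concern that prompted the rule. The change should be made before the rule is applied to anyone, so that no participant's data are set aside in the meantime.
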